#### 9.4 Anticipated Benefits to Participants

There may be no benefit to individuals who participate in this study. However, participants who have defaulted from the national program may benefit from being followed up by trained study staff and may decide to re-engage in care following phone contacts or home visits. Participants receiving study-supported maternal viral load or infant DNA PCR or rapid HIV testing may receive the benefits of early detection of treatment failure or infant HIV infection. Finally, if the study reveals ways to improve CFL services or MIP retention along the PMTCT care continuum, then future patients, and in some cases the individuals providing data themselves, may benefit.

#### 9.5 Participant Compensation

As nested cohort study activities are intended to reinforce and in some cases enhance the existing standard of care, and will take place once, aligned with the schedule of routine care, compensation will follow local recommendations of providing the Malawi Kwacha equivalent of \$4. Because in-depth interviews may take 1 hour or more to complete, these individuals will be reimbursed the Malawi Kwacha equivalent of \$4 for their time and travel expenses. Lastly, since FGDs will last 1 to 2 hours, and in many cases will require travel to a central location in the district, travel reimbursement in the Malawi Kwacha equivalent of \$4 will be provided to FGD participants.

#### 9.6 Safety Monitoring and Unanticipated Problems

Unanticipated problems involving risks to study participants refers to any incident, experience, or outcome that:

- Is unexpected (in terms of nature, severity, or frequency) given the research procedures that are described in the protocol-related documents, such as the IRB-approved research protocol and consent documents;

- Is related or possibly related to an individual's participation in the research; and
- Suggests that the research places participants or others at a greater risk of harm (including physical, psychological, economic, or social harm) related to the research than was previously known or recognized.

Given the observational nature of this implementation research study and the minimal risks involved with participating, we do not foresee any unanticipated problems taking place. Because we will be enhancing the standard of care for nested cohort participants by tracing patients who have disengaged from HIV care, and by offering viral load and EID testing for mother-infant pairs, we feel the risks associated with participation can be categorized as minimal. Nevertheless, the study PI and co-investigators will be vigilant in reviewing study data to ensure participant safety. We will put into place a data and safety monitoring plan that calls for regular review of study data by the PI and the study manager, [name], who is an accomplished Malawian clinician with years of experience caring for MIPs in the Malawi HIV and PMTCT programs and helping develop national guidelines. The PI and [name] will review compiled data on nested cohort participants at regular intervals, particularly quantitative maternal and infant HIV-1 viral load and infant EID test results, to look for evidence of virological failure among ART-treated mothers and infants, and new HIV diagnoses among HEIs, which are expected to be the most common adverse events. Any mother or infant found to have a viral load over 1,000 copies/ml will be referred to the nearest MOH health facility for intensive adherence support counseling and clinical evaluation for repeat viral load testing and potential switch to second-line ART in accordance with national HIV guidelines. Similarly, any HEI identified with new HIV infection will be referred to the nearest MOH health facility for clinical evaluation and immediate ART initiation per national guidelines. All cases of suspected social harm will be documented on a case reporting form, reviewed by the study PI, mitigated directly whenever possible, and reported to all local and international regulatory bodies. All study staff will be trained to follow a study standard operating procedure detailing how to activate existing, routine referral mechanisms in all cases where a participant is suspected of being in need of medical attention or psychosocial support. In all instances, we will look to leverage our existing robust collaborations with MOH health facilities, CFL programmes, and other non-governmental implementing partners built over 20 years of UNC Project's presence in Malawi to strengthen HIV diagnostic and monitoring services, promote participant engagement in HIV care, and enhance the existing standard of care.

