#### *6.5.2.3.6 Nested Cohort Exposed Infant Biological Outcome Ascertainment*

For HEIs of maternal nested cohort participants, study staff will support routine EID testing procedures at MOH ART/HCC clinics in selected districts according to national guidelines. Thus, for HEIs over 6 weeks but under 12 months of age who are without a documented DNA PCR test result at the time of study field activities, we will collect a routine DBS sample for “catch up” DNA PCR testing to be performed through the existing MOH EID testing system. Similarly, for HEIs 12 months of age and older without a documented HIV rapid test result, we will support “catch up” infant rapid HIV serological

testing through review of existing MOH records and referral of HEIs with unknown status for HIV testing services (HTS).

For HEIs of nested cohort participants who are over 6 weeks but under 12 months of age, and who have previously undergone MOH EID testing but who are without a documented HIV test result within about 3 months of their mother's study encounter, we will collect 1 DBS card sample (i.e. 5 wells of 50 µL each or 250 µL total) following MOH-recommended collection procedures for study-specific DNA PCR testing to be done at the UNC Project Tidziwe Laboratory in Lilongwe. For HEIs 15 months of age or older who have not received routine HIV testing within about 3 months of their mother's study encounter, study staff will conduct study-specific HIV rapid antibody testing in accordance with MOH HTC procedures.

In all cases, we will follow MOH guidelines for HIV testing, including the preparation, collection, handling and transport of DBS samples for EID testing. All EID DNA PCR test results will be returned to the clinic from which the HEI was originally identified. We will subsequently inform all mothers that their HEI's test results are ready and have been submitted to the clinic. We will recommend they return to discuss these results with the clinic healthcare providers. This will support good clinical care and will also provide additional encouragement to those disengaged/ defaulted from care to re-engage.

Due to the dispersion of HEI ages at the time of maternal and infant enrolment in the nested cohort, it will not be possible to ensure testing at a pre-specified age. We will adjust for any variability in timing of HIV testing during the analysis phase (*see section 7.0 below*).

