#### *6.5.2.3.7 Routine Care and Treatment for Maternal and Infant Nested Cohort Participants*

As we are proposing an observational study without intervention, routine HIV treatment and care for MIPs enrolled in the nested cohort will continue to be provided by MOH HCWs at MOH facilities according to standard clinical practice, in strict accordance with the Malawi Ministry of Health integrated PMTCT/ART guidelines.

Specifically, as part of routine clinical care, all pregnant women will receive the following standard services from the MOH per national guidelines: All pregnant women will receive HTS using the opt-out method at their first ANC visit. All pregnant women diagnosed with HIV infection will undergo ART education and counselling and confirmatory HIV testing prior to starting first-line regimen 5A

(TDF/3TC/EFV) as soon as possible. Women with a documented contraindication to 5A (e.g. renal failure or psychosis) will start an alternative regimen in accordance with national guidelines. Maternal prophylaxis will include cotrimoxazole (CPT) and isoniazid preventive therapy during pregnancy and thereafter per national guidelines. HIV RNA will be measured at 6 and 24 months post ART initiation, and every 2 years thereafter or in the event of clinical suspicion of treatment failure based on new WHO Stage 3 or 4 condition after more than 12 months on ART. Mothers will be seen monthly for 6 months after the initial ANC visit and then quarterly per Malawi HIV program recommendations.

As part of routine care provided by the MOH, all HEIs will be enrolled in the national HIV Care Clinic and will receive 12 once-monthly follow-up visits as detailed on the national pink card. HEIs will also receive nevirapine prophylaxis, CPT, HIV testing services, feeding counselling, and immunization services per national guidelines.

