#### **Secondary Outcomes:**

- Proportion of pregnant women newly registered in ANC who received HIV testing services
- Proportion of HIV-infected PMTCT clients initiated on anti-retroviral therapy
- 6-month post-ART initiation retention in care for HIV-positive mothers
- Proportion of HIV-positive mothers achieving HIV virological suppression from 6 months post-ART initiation (at MOH-recommended times of 6 and 24 months post-ART and, through the study, at time points between 12 and 24 months post-ART initiation)
- 12-month infant HIV-free survival
- Exposed infant “early” HIV infection status (i.e. HIV-1/2 DNA PCR result) from age 6 weeks
- 24-month child HIV-free survival
- 12- and 24-month infant HIV sero-status
- Median time from PMTCT enrolment to maternal ART initiation
- Median age of ART initiation for HIV-infected infants and young children
- Proportion of HIV-infected infants and young children achieving HIV virological suppression (from 6 months post-ART initiation per MOH guidelines)

- Proportion of HIV-infected mothers and infants who “returned to care” within 30 and 60 days of meeting the national ART program definition of loss to follow-up/ “defaulting” (i.e. not known to have transferred out, stopped or died AND have not returned to the clinic for 2 months after the woman is expected to have run out of ARVs).
- Proportion of HEIs who “returned to care” within 30 and 60 days of meeting the national HIV Care Clinic (HCC) programme definition of loss to follow-up/ “defaulting” (i.e. not known to have transferred out, stopped or died AND have not returned to the clinic for 2 months after the “next appointment date” given at the last HCC visit).

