Proportion of infants/ young children receiving anti-retroviral therapy (i.e. “Infant ART Initiation”):

Similar to the related maternal indicator, for this infant ART initiation indicator, we will calculate the proportion of HIV-infected infants/ young children initiating ART during the 12 months preceding the evaluation day among all infants with a documented positive HIV test/ evidence of being HIV-positive before the day of evaluation.

Proportion of PMTCT mothers and infants/young children who started ART and have a suppressed HIV

viral load (“Viral suppression”): Using viral load test result data, we will calculate and present separately the proportion of ART-initiated, HIV-infected mothers and ART-initiated HIV-infected infants/ young children who achieved viral suppression. For this final step of the cascade (i.e. the “third 90”), we will use the numerators from the maternal and infant ART initiation indicators for our respective denominators, and will assess the subset of these denominators with documented suppressed viral load test results within 12 months of the evaluation day. We will define viral suppression using a number of established thresholds for HIV-1 viral load, including less than 20 copies/ ml (the lower limit of detection for VL testing performed on plasma collected by venipuncture), less than 550 copies/ml (the lower limit of detection for VL testing performed on DBS) and less than 1,000 copies/ml (the definition of viral suppression used in the recent MOH Malawi Population-Based HIV Impact Assessment).

*7.2.2.3 Maternal IDI Data*

For qualitative data, the same analytical approach will be employed as described for Objective 1 above, except that we will search for patterns in the data that help explain client experiences with CFL model services and navigating the PMTCT care continuum for mothers and their children.

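### The infant ART-initiation indicator can credit a care model with treatment starts prompted by the study's own testing and referral, which can shrink a real gap between models

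*Protocol*

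**What the plan says.** Section 6.5.2.3.6 provides for catch-up testing of infants without a documented result. It adds study-specific tests for infants without a recent one: DNA PCR below 12 months and, from 15 months, "study staff will conduct study-specific HIV rapid antibody testing in accordance with MOH HTC procedures". On PCR results it says "All EID DNA PCR test results will be returned to the clinic from which the HEI was originally identified". Section 9.6 adds that "any HEI identified with new HIV infection will be referred to the nearest MOH health facility for clinical evaluation and immediate ART initiation".

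Section 7.2.2.2 builds the infant ART-initiation indicator from the full cohort enriched by nested-cohort data, and compares it across CFL models and SOC. The numerator is "the proportion of HIV-infected infants/ young children initiating ART during the 12 months preceding the evaluation day", taken "among all infants with a documented positive HIV test/ evidence of being HIV-positive before the day of evaluation". The evaluation day is given by example, under the known-status indicators, as the last day of study activities in the district. Section 7.2.2.1 corrects all estimates from the sampled pairs by inverse-probability weights.

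Section 6.5.2.3.7 states that "we are proposing an observational study without intervention", while section 9.6 says that tracing and testing improve on the standard of care for nested-cohort participants. No section distinguishes a programme-prompted ART start from a study-prompted one. Section 7.1 also lists "Median age of ART initiation for HIV-infected infants and young children" as a secondary outcome.

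**The concern.** The indicator is meant to show how well each model gets infected infants onto treatment under routine conditions. Its window closes after the study has traced, tested and referred in the same district. A model with weaker routine follow-up leaves more infected infants for the study to find. If those infants start ART before the window closes, they enter numerator and denominator together, and the weaker model is lifted more than the stronger one. The planned comparison would then depend partly on how early in fieldwork a site was visited and how fast referral worked.

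This comes from the definition as written, because section 7.2.2.2 itself fixes the numerator, the denominator and the window. It is more than a detail left for later.

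**Working it through.** The protocol states no figure for this effect, so there is none to reproduce. The check is an illustration.

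**Scale, from protocol inputs.** Section 6.4 plans 1,192 infants (894 CFL, 298 SOC) and uses 7% infected by 12 months.
- All: 0.07 × 1,192 = 83.4
- CFL: 0.07 × 894 = 62.6
- SOC: 0.07 × 298 = 20.9

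The protocol does not say how many infections the programme would miss. Section 2.0 gives 21% and 36% of exposed infants out of care at 12 and 24 months. Used only as a rough proxy, these give 83.4 × 0.21 = 17.5 to 83.4 × 0.36 = 30.0 study-found infants in the nested cohort, before weighting. Out of care is not the same as undiagnosed, so this shows order of magnitude only.

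**Indicator.** Let
- d = share of infected infants found by the programme,
- s = share of programme-found infants with a counted ART start,
- t = share of study-found infants who start, with the start recorded, before the evaluation day.

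Programme starts over all infants found infected = d·s.
Indicator as defined = d·s + (1 − d)·t.
Gap between models A and B as defined = (d_A − d_B)(s − t).

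Assumed inputs, none from the protocol: s = 0.9, d_A = 0.90, d_B = 0.64. Programme only: A = 0.90 × 0.9 = 81.0%, B = 0.64 × 0.9 = 57.6%, gap 23.4 points.

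| t | A as defined | B as defined | Gap (points) |
|---|---|---|---|
| 0 | 81.0% | 57.6% | 23.4 |
| 0.5 | 81.0 + 0.10 × 50 = 86.0% | 57.6 + 0.36 × 50 = 75.6% | 10.4 |
| 0.9 | 90.0% | 90.0% | 0 |
| 1.0 | 91.0% | 93.6% | −2.6 |

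The gap closes when t = s and reverses above that. The 12-month numerator window can lower s, because an early programme start can fall outside it while the child stays in the denominator. The gap then closes at a lower t.

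**Weighting.** The within-site factor in section 7.2.2.1 runs from 1/(80/100) = 1.25 to 1/(10/100) = 10. One study-prompted start therefore stands for 1.25 to 10 infants at the site, before the site and participation factors. Section 6.5.2.2 says that staff have no direct contact with unsampled pairs, so those infants could not have been tested or referred by the study. Weighting numerator and denominator alike does not by itself enlarge the percentage-point bias. It does make the estimate describe detection and treatment that the uncontacted infants did not receive.

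**The case against.** The strongest reply is that the protocol nowhere says these starts count. The nested-cohort encounter is one-time (section 6.5.2.3.1), and no later re-abstraction of infant ART start is described. PCR results go back to the clinic and mothers are advised to return, so a start may fall after the evaluation day or never be captured. That child then sits in the denominator only, and the missed infection shows in full. This stands: it is the t = 0 row. It makes the effect conditional without removing it, since a rapid test gives a same-visit result and fieldwork in a district may continue after it. The evaluation day is also given only as an example, but no other day is offered.

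It can also be said that without study testing the missed infants would not be in the denominator at all. That is true: on routine records alone, both models in the illustration would show s = 90%. Study testing reveals the gap, which is why those infants should stay in the denominator without their study-prompted starts being credited.

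The stakes are limited. This is a cascade measure resting on about 21 expected infected infants in SOC, and the primary outcome, maternal 12-month retention, is untouched.

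A reader might infer two stronger things. The first is that the treated proportion rises by 21 to 36 points and every model approaches 100%. That would treat attrition at two ages as two models' missed-infection rates and assume complete treatment of all infants found. The protocol supports neither step.

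The second is that differences in median age at ART initiation are masked as well. Late study-found starts raise the median in the model that misses more. Suppose that programme starts are uniform over 1.5 to 12 months, study-found starts fall at 12 to 24 months, and 90% or 64% of starters are programme-found. The pooled median is then 1.5 + 10.5 × 0.5/0.90 = 7.3 or 1.5 + 10.5 × 0.5/0.64 = 9.7 months, against about 6.7 for programme starts alone. The weaker model looks worse.

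**Conclusion.** The point holds for the infant ART-initiation indicator in section 7.2.2.2. As defined, it admits starts prompted by the study's own testing and referral, credits them to the model that missed the infant, and carries them by weighting to infants the study never contacted. The effect requires the start to occur and be recorded before the evaluation day. With the assumed inputs above, a 23.4-point gap becomes 10.4 points at t = 0.5 and zero at t = 0.9, and stays at 23.4 if no start is recorded in time. The protocol fixes neither the true gap nor t, so these figures show direction and possible size and are not forecasts.

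For median age at ART initiation, the documents support only a narrower remark: the date of the study visit partly sets the age of study-found starters. The correction should be made, but it does not bear on the main conclusion of the study.

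**What to change.** Leave the referral in section 9.6 as it is. In section 7.2.2.2:
- Count an infant ART start in the numerator only if it is dated before the pair's first study contact. Contact is a safer cut-off than the test, because sections 6.5.2.3.3 and 6.5.2.3.8 have staff encourage women who have dropped out to return to care. Pairs never contacted keep the evaluation day.
- Keep infants first found positive by study or study-supported catch-up testing in the denominator, as not on ART.
- Report study-prompted starts separately.
- State which numerator supplies the denominator of the infant viral-suppression indicator, which is defined from it.

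For median age at ART initiation in section 7.1, do not drop starts after study contact. That would remove late starters and favour models that miss infants. At most, flag the study-prompted starts and report them separately.

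The cost is analysis wording and a flag for source of diagnosis. Section 6.6.3 already lists HIV test dates and ART start dates; the date of first study contact must be logged. The main indicator no longer depends on capturing starts after the encounter, although the separate report does. The reported infant ART proportion will be lower, and slightly understated where the programme would have found a child between first contact and the evaluation day.

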
### 9.7 Study Discontinuation

This study may be discontinued at any time by the sponsors, the Ministry of Health, or UNC as part of their duties to ensure that research participants are protected. Individual-level study data will only be used for analyses related to this study; summary statistics and de-identified aggregate data may be used to improve routine service delivery in study districts. UNC Project—Malawi, UNC, and protocol-affiliated investigators and staff members will not use study data for other, unrelated analyses without the express permission of the MOH.

### 9.8 Regulatory Review

This protocol will be reviewed by the National Health Sciences Research Committee of Malawi (NHSRC) and the Biomedical Institutional Review Board of the University of North Carolina at Chapel Hill, USA (UNC IRB). Co-investigators from other institutions will establish reliance agreements, as applicable, to have their institutions follow guidance provided by NHSRC and UNC IRB. All study procedures will conform to U.S. and Malawian ethical standards regarding research involving human participants and will follow international guidelines for Good Clinical Practice.

## 10.0 Capacity Strengthening

Continuing UNC's track record for building local research capacity in Malawi, we envision this study as a platform to engage junior Malawian investigators more deeply in operational research and implementation science. We will accomplish this by leveraging UNC Project—Malawi's existing Fogarty Global Health Training Program in HIV implementation science to identify promising Malawian trainees who can engage meaningfully in the research described herein by way of a relevant sub-study or secondary analysis using data generated from this proposal. This study will also support [name] (the senior analyst on this study) and other junior Malawian investigators in their career development, providing valuable preliminary data and small grant opportunities to develop their research skills and to pursue independent research funding.

